#### Self-reported outcomes

Analyses will focus on comparisons between the responses of the BC-Predict and NHSBSP groups at 6 months follow up, controlling for baseline responses and baseline patient characteristics. We will use ANCOVA, first with baseline responses to the same questionnaires as covariates, secondly treating both baseline and 6-month responses as related endpoints, using hierarchical linear models. Out of the available self-reported outcomes, we have selected the primary outcome to be anxiety (State Trait Anxiety Inventory) at 6-months, but we will also examine effects on all measures included in Table 1, as well as effects at 3 months. We will use the variables concerning knowledge, and attitudes to screening, as well as screening attendance, to assess the extent to which decisions to attend screening are informed, in line with a standard approach to assessing this [17]. The measures of health status (EQ. 5D-5 level) and capability (ICECAP-A) will be converted to preference weights using published algorithms [40] and population tariffs [41], as appropriate.

In addition to providing information about potential harms of BC-Predict, secondary analyses will examine whether women who are randomised to receive questionnaires differ in terms of uptake of screening or BC-Predict. This will inform about the likelihood of biases being introduced by comparisons of questionnaire responses in a possible subsequent definitive trial.

The sample size calculation is based on the six-item short-form of the state scale of the State Trait Anxiety Inventory [29], which measures general anxiety currently experienced on a scale of 20 to 80. Previous research in England with women invited to breast cancer screening found a mean state anxiety score of 37 [42]. A score of 49 has been found in patients with a diagnosis of anxiety disorder [43].

Assuming a two-tailed independent samples t-test, then *n* = 1054 (*n* = 527 women per experimental group) will be required to have 90% power (with α = 0.05) to detect a small standardised difference of d = 0.2. This equates to a difference between adjacent response categories (e.g. “not at all” and “somewhat”) on 2.5 of the 20 items on the full form of the scale. We anticipate that asking 1054 women per group will result in responses from *n* = 527 women per group being obtained at both baseline and 6 months, assuming a 70% response rate on both rounds.

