All BC-Predict participants will have been invited for breast screening but a proportion may choose not to attend their breast screening appointment; attendance at breast screening mammogram is not a compulsory part of the study. The Participant Information Sheet explains that participants’ mammographic breast density will be included in their risk assessment, providing they attend their mammogram within 6-weeks of their first offered appointment. It is also explained that including mammographic density increases accuracy of the risk assessment. Any participant who declines a mammogram or has a mammogram after this time will not have this data included in their risk assessment, which is explained in their risk feedback letter.

To assess self-reported harms and benefits, and to inform an economic analysis, a randomly selected subsample of *n* = 2108 women (*n* = 1054 each from usual care NHSBSP and BC-Predict) will be asked to complete questionnaires assessing psychological benefits and harms of BC-Predict at baseline, 3-months and 6-months. For women in both groups, the request to complete the questionnaire will be sent shortly after their mammography invitation but before their first offered mammogram appointment, asking for their help in evaluating a new approach to providing NHS breast screening. They will be given instructions to complete an online consent form and questionnaire using their unique study identification number on SmartSurvey (https://www.smartsurvey.co.uk/). The same women will be asked to complete the questionnaire three and 6 months after their first offered mammogram appointment. Women in both experimental groups will only receive follow-up questionnaires once they receive a clear mammogram result.

The risk assessment and feedback will take account of each patients’ journey through the NHSBSP. The study team will periodically check screening outcomes for participants. There are a number of initial screening outcomes: (a) clear mammogram and woman will be invited for routine breast screening in three-years (routine recall); (b) mammogram taken is technically inadequate so repeat mammogram is required (technical recall); (c): suspicious mammogram and further assessment required (recall for assessment). For all scenarios the GP will be informed of the participant’s involvement in the study and provided with their risk feedback.

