Participants who are confirmed as having a routine recall screening outcome will receive their risk feedback after this, approximately 6 weeks after their mammogram. Participants who are invited for a technical recall/recall for assessment appointment, and attend this appointment within 6 months of their first scheduled technical recall/recall for assessment appointment, and who are subsequently confirmed as not having breast cancer will receive a risk feedback letter following confirmation of an absence of breast cancer. Participants who are invited for a technical recall or recall for assessment appointment but do not attend within 6 months of the first scheduled technical recall/recall for assessment appointment (i.e. those for whom there is no screening outcome within 6 months of initial screening outcome) will receive their risk feedback 6 months after joining BC-Predict.

Participants who do not attend a breast screening appointment within six-weeks of their first offered breast screening appointment will receive their risk feedback after this six-week period (i.e. 7 to 8 weeks since their first offered breast screening appointment).

Participants who are diagnosed with breast cancer will not receive a standard risk feedback letter. Participants will be sent a letter 1 year after diagnosis which will offer them feedback from the study. If they opt to receive this, they will be sent a personalised letter explaining their breast cancer risk factors.

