#### Self-reported outcomes

The self-reported measures of potential harms and benefits of BC-Predict to be completed by a sub-sample of participants are shown in Table 1.

**Table 1 Tab1:** Self-reported measures to be assessed, at each of the three timepoints.

Baseline	3 months	6 months
State Anxiety [29]	State Anxiety [29]	State Anxiety [29]
Cancer Worry [30]	Cancer Worry [30]	Cancer Worry [30]
Risk perceptions [31]	Risk perceptions [31]	Risk perceptions [31]
Attitudes to screening [32]		Attitudes to screening [32]
Knowledge [33]		Knowledge [33]
Intention (future screening) [32]	Intention (future screening) [32]	Intention (future screening) [32]
Health status (EQ-5D5L) [34]	Health status (EQ-5D5L) [34]	Health status (EQ-5D5L) [34]
Capability [35]	Capability [35]	Capability [35]
	Satisfaction with information [36]	Satisfaction with information [36]

**Informed choices regarding screening will be estimated from attitudes to screening at baseline, knowledge and screening attendance, using a standard approach* [17]

***Women invited to BC-Predict will receive the above. Women invited to NHS-BSP will receive the above minus the satisfaction with information questionnaire*

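### Both models named for 6-month anxiety omit the 3-month score, so their agreement cannot reveal selective loss after the risk letter

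*Protocol article*

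**What the plan says.** All places are in the protocol article.

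- **Outcome** (Analysis plan and power calculations, Self-reported outcomes): "we have selected the primary outcome to be anxiety (State Trait Anxiety Inventory) at 6-months".
- **First model** (same section): "We will use ANCOVA, first with baseline responses to the same questionnaires as covariates".
- **Second model** (same section): "secondly treating both baseline and 6-month responses as related endpoints, using hierarchical linear models".
- **Role of the 3-month data** (same section): "we will also examine effects on all measures included in Table 1, as well as effects at 3 months". They are examined as a further comparison and enter neither 6-month model.
- **Collection**: Table 1 lists state anxiety at baseline, 3 and 6 months. Under Procedure: "The same women will be asked to complete the questionnaire three and 6 months after their first offered mammogram appointment". The baseline request goes out before the first offered appointment.
- **Risk letter** (Procedure): "Participants who are confirmed as having a routine recall screening outcome will receive their risk feedback after this, approximately 6 weeks after their mammogram". The Background gives 6 to 8 weeks.
- **Expected response**: 527 women per group "being obtained at both baseline and 6 months, assuming a 70% response rate on both rounds".

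**The concern.** Increased state anxiety is one of the harms the study sets out to quantify. Baseline is measured before the letter. For a woman who answers at 3 months but not at 6, the 3-month score is normally the only anxiety measure taken after she learned her risk.

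The ANCOVA drops this woman. The two-occasion hierarchical model keeps her baseline but can predict her 6-month score only from that baseline. Both are valid only if, given group and baseline, loss at 6 months is unrelated to anything that happened later. Adding the 3-month score relaxes this: loss may then also depend on 3-month anxiety.

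Because the two named models share the assumption, finding the same answer from both could be read as robustness when it is not. The occasions in the model are written into the article, so this is a stated choice and not a detail left to a fuller document.

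**Working it through.** **1. The plan's own figures.** For d = 0.2, 90% power and two-sided 5%: n = 2 × (1.960 + 1.282)² / 0.2² ≈ 525 per group by the normal formula, and 526.3, so 527, by the exact t-test. The stated 527 reproduces. Applying the response rates, 1054 × 0.7 × 0.7 = 516, 2% below 527, with power 0.895. That shortfall is immaterial.

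**2. Size of the loss.** Baseline responders: 1054 × 0.7 ≈ 738 per group. Missing at 6 months: 738 × 0.3 ≈ 221 per group.

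**3. Timing.** Baseline comes before the appointment, the letter about 6-8 weeks after the mammogram, and the questionnaires at 3 and 6 months (about 13 and 26 weeks) after the first offered appointment. For most letter recipients the order is baseline, letter, 3 months, 6 months. After a recall the letter can come later.

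**4. Simulation with complete 3-month data.** From the plan: 738 baseline responders per group and a true 6-month effect of 0.20 SD. Assumed, because the article does not give them: correlation 0.5 or 0.7 between all occasions, a 3-month effect of 0.20 SD unless stated, and logit P(loss at 6 months) = -1.0 + k × anxiety in SD. This gives 66-74% response. There were 600 replicates, with Monte Carlo error about 0.002. Ranges cover both correlations.

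| Loss depends on | k usual care / BC-Predict | ANCOVA and baseline + 6-month model | Baseline + 3-month + 6-month model |
|---|---|---|---|
| nothing | 0 / 0 | 0.20 | 0.20 |
| 3-month anxiety, equally | 0.5 / 0.5 | 0.20 | 0.20 |
| same, 3-month effect 0.4 SD | 0.5 / 0.5 | 0.195-0.196 | 0.20 |
| 3-month anxiety, BC-Predict only | 0 / 0.5 | 0.16-0.17 | 0.20 |
| 3-month anxiety, BC-Predict only | 0 / 1.0 | 0.12-0.14 | 0.20 |
| opposite direction, BC-Predict only | 0 / -0.5 | 0.225-0.23 | 0.20 |
| 6-month anxiety itself, BC-Predict only | 0 / 0.5 | 0.09-0.125 | 0.11-0.14 |

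The ANCOVA and the two-occasion model agreed within 0.002 SD in every row.

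**5. Simulation with incomplete 3-month data.** Response at 6 months was set to 70%, the 3-month/6-month correlation to 0.5-0.7 and the baseline correlations to 0.5. Arms were large (200,000 each), and 90% of 6-month responders were assumed to answer at 3 months. Loss depends on 3-month anxiety in BC-Predict only, with log-odds 0.3-0.5 per SD. Since exp(-0.3) = 0.74 and exp(-0.5) = 0.61, each SD lowers the odds of response by 26-39%.

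- Two-occasion estimate: about 0.13-0.18 instead of 0.20.
- Three-occasion estimate: 0.19-0.20 if 70% of the women lost at 6 months answered at 3 months, but only 0.15-0.18 if 20% did.
- Equal dependence in both groups: about 0.20 from either model.

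**6. Consequence.** A shortfall of 0.02-0.07 SD is 10-35% of the design effect. At 527 per group, t-test power is 90% for 0.20, 83% for 0.18 and 56% for 0.13. The article equates 0.2 SD with one-category shifts on 2.5 items, about 2.5 points on the 20-80 scale. The shortfall is then about 0.25-0.9 points.

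**The case against.** A reader might infer that the planned analysis will understate harm. The article does not support that. It assumes the same 70% response in both groups and says nothing about who stops responding. Equal dependence on anxiety leaves a bias of 0.005 SD or less, and the opposite pattern overstates harm by about 0.025-0.03 SD. Only about 8,000 of 18,700 invited women (43%) are expected to take up BC-Predict, which would dilute any letter-related difference in loss. This objection stands, so the direction has to be conditional.

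The 3-month data are also not ignored. Effects at 3 months will be examined, and women who answer then but not at 6 months are included there, so early anxiety could still show. That stands too, but a separate 3-month comparison does not correct the 6-month estimate, which is the primary one.

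The remedy has limits. It helps little if the women lost at 6 months mostly missed 3 months as well, or if loss follows the unseen 6-month score. The article gives no 3-month response rate. This stands and calls for an added sensitivity analysis.

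Finally, baseline-adjusted ANCOVA is a standard analysis for a single-time-point outcome, missing-data handling often sits in an analysis plan that is not shown, and this is a feasibility study. These are reasons not to demand that ANCOVA be replaced. They do not justify limiting an already planned hierarchical model to two occasions when a third is collected.

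**Conclusion.** The point holds as an exposure to bias, not as a demonstrated bias. Both named 6-month models omit the 3-month score, give practically the same estimate, and cannot detect or correct loss driven by anxiety after the letter.

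If such loss is stronger in BC-Predict than in usual care, the estimate moves towards no harm. Under log-odds of 0.3-0.5 per SD in BC-Predict only, it is about 0.13-0.18 SD instead of 0.20. These log-odds, the correlations and the share of lost women who answered at 3 months are assumptions; only the 0.2 SD, the 1054 women and the 70% response come from the article. The flat conclusion that harm is understated would need evidence of loss that differs by group in this direction, and the article offers none.

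**What to change.** In Analysis plan and power calculations, Self-reported outcomes:

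1. Have the hierarchical model treat baseline, 3-month and 6-month responses as related endpoints, with group by time terms, unstructured covariance and all available responses.
2. Report its 6-month group contrast alongside the baseline-adjusted ANCOVA.
3. Do the same for the other Table 1 measures collected at all three times: cancer worry, risk perceptions, intention, EQ-5D-5L and capability.
4. Add a simple not-missing-at-random sensitivity analysis, for example shifting the unobserved 6-month scores by a range of amounts that may differ between groups, because the three-occasion model corrects only part of the problem in the cases named above.

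The cost is a change of wording and a little extra analysis on data already collected. No additional women, contacts or questionnaires are needed.

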### Analysis plan and power calculations

#### Core outcomes

In total, approximately *n* = 18,700 women will be offered BC-Predict and *n* = 18,700 will be offered usual care NHSBSP over the total 16-month period. Based on the recruitment rate in PROCAS, *n* = 18,700 women being offered BC-Predict should result in 8000 women taking it up. The attendance rate to usual NHSBSP in Greater Manchester is 69% [5, 10].

Core outcomes will be compared for cohorts of women who are invited to BC-Predict and those who are invited to usual care (NHSBSP). Thus we will have in excess of 8000 participants in BC-Predict and NHSBSP groups for both comparisons: (a) within-site and (b) between sites over the same time period. The primary outcomes are binary. Logistic regression will be the primary statistical analysis method. We shall assess heterogeneity effects using interaction tests in the logistic regression, to examine differences in outcomes by time or location or screening type (prevalent v incident). Even in the presence of geographic or temporal heterogeneity of the effect, or of carryover effects continuing beyond the crossover period, we will still have sufficient data for a valid and fully powered comparison.

For core outcomes 1 and 2, we are interested in equivalence, in that we anticipate that invitation to BC-Predict will not substantially affect screening attendance. With 18,700 women in each group we will have in excess of 90% power to establish equivalence, defined as a 95%CI on the difference which does not exceed ±5% on the attendance rate at first offered appointment, if the latter is around 50% [37]. Similarly, we will have more than 90% power for the same comparison for eventual attendance within 180 days if the latter is around 70%.

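### The expected 527 questionnaire completers per group ignore the rule that follow-up goes only to women with a clear mammogram, and that rule removes women who get a risk letter without attending

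*Protocol article*

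**What the plan says.** Protocol article, Analysis plan and power calculations, Self-reported outcomes: the primary self-reported outcome is state anxiety at 6 months. The sample size is set as follows: "Assuming a two-tailed independent samples t-test", 527 women per group give 90% power "to detect a small standardised difference of d = 0.2". Asking 1054 per group is expected to produce those 527, with responses "being obtained at both baseline and 6 months, assuming a 70% response rate on both rounds". The planned analysis is ANCOVA with the baseline response as covariate, followed by hierarchical models.

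Procedure: the baseline request is sent after the screening invitation and before the first offered appointment. The later questionnaires are timed at 3 and 6 months from that appointment date, but with a condition: "Women in both experimental groups will only receive follow-up questionnaires once they receive a clear mammogram result".

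Core outcomes, power paragraphs: "The attendance rate to usual NHSBSP in Greater Manchester is 69" per cent; attendance within 180 days is taken as around 70%.

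Procedure, on risk feedback: a mammogram is not compulsory for BC-Predict participants. "Participants who do not attend a breast screening appointment within six-weeks of their first offered breast screening appointment will receive their risk feedback" once that window has closed. Women recalled who do not attend within 6 months are also sent their risk feedback.

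**The concern.** The sample-size paragraph treats non-response as the only source of loss. The Procedure section adds a second one: a baseline responder who does not attend, or has no clear result, is never sent the follow-up questionnaire. The two sections do not agree on how many women can contribute at 6 months.

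What is at stake goes beyond the count. Screening attendance is core outcomes 1 and 2, and lower screening uptake is listed among the potential harms. The self-reported comparison is therefore made in a subset defined by behaviour that the intervention might change. BC-Predict participants who receive a risk letter without a clear mammogram have received the element that might cause distress, yet they are outside the 6-month anxiety, worry and EQ-5D comparison. The economic analysis takes its EQ-5D-5L and ICECAP-A data from the same questionnaires.

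**Working it through.** **Inputs from the protocol:** 1054 asked per group; 70% response at each of two rounds; d = 0.2, two-sided α = 0.05, 90% power, 527 required per group; 69% attendance among invitees to usual screening in Greater Manchester; 8000 of 18,700 expected to take up BC-Predict.

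**Assumed, because not given:** the proportion *a* of baseline responders who attend and have a clear result (69% to 100%), and the correlation *r* between baseline and 6-month anxiety.

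**1. The plan's own figures.** Solving the two-sample t-test for 90% power gives 526.3, so 527 per group is right. The yield from response alone is 1054 × 0.70 × 0.70 = 516. That is 2% below 527 and costs about half a point of power (89.4% against 90.0%). A response of 70.7% on each round would give exactly 527, so this gap is minor.

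**2. Adding the clear-mammogram condition.** Yield = 516.5 × *a*. Power is approximately Φ(0.2 × √(n/2) − 1.96). For ANCOVA the standard deviation is multiplied by √(1 − r²).

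| *a* | Yield per group | t-test power | ANCOVA, r = 0.3 | ANCOVA, r = 0.5 |
|---|---|---|---|---|
| 69% | 356 | 76% | 80% | 87% |
| 80% | 413 | 82% | 85% | 91% |
| 90% | 465 | 86% | 89% | 94% |
| 100% | 516 | 89% | 92% | 96% |

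As an example, at *a* = 69%: 0.2 × √(356.4/2) = 2.67; 2.67 − 1.96 = 0.71; Φ(0.71) = 0.76. With r = 0.6 the ANCOVA power at 356 would be about 92%.

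**3. Could the second 70% already include women who are not sent a questionnaire?** Response among those who are sent one would then have to be 0.70/*a*: 78% at *a* = 90%, 87.5% at 80%, and 101% at 69%, which is impossible. The text does not state this reading.

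**4. Women left out.** Baseline responders per group: 1054 × 0.70 = 738. At 69% attendance, non-attenders number 738 × 0.31 = 229. Expected BC-Predict uptake is 8000/18,700 = 43%. If it is the same among non-attending responders, 229 × 0.428 = 98 women in the BC-Predict group would receive a risk letter and no follow-up questionnaire. At 90% attendance the same sum is 738 × 0.10 × 0.428 = 32. Women recalled who do not attend would add to this; their number cannot be derived from the documents.

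**The case against.** Several points on the other side stand.

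- The 69% describes everyone invited in Greater Manchester, while the sites also include East Cheshire and East Lancashire. Women who have already consented and returned a screening questionnaire may well attend more often. The figure of 356 is the low-end scenario, and the protocol does not imply it as the expected yield.
- A reader might infer that the anxiety comparison is underpowered. The documents do not establish that. The t-test figure is conservative for a planned ANCOVA, and with r = 0.5 power passes 90% once *a* reaches 80%. It falls short with lower correlations or lower attendance.
- A reader might also infer that women put off screening go uncounted. They do not: attendance is compared across all 18,700 per group. Only the self-reported outcomes lose them.
- Some non-attenders may be reached elsewhere. Sub-study three sends the 6-month questionnaire to every woman at low risk in the final four months, and the interviews sample all risk groups; neither states an attendance condition. Neither replaces the comparison in the randomly selected subsample.
- The condition is the same in both groups, and the protocol expects no substantial effect on attendance. Differential selection is possible, but nothing in the documents allows it to be sized, and it may be small.

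None of this removes the mismatch between the two sections, or the missing follow-up of women who receive letters without a clear result.

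**Conclusion.** The point holds in limited form. At the stated response rates, 1054 asked per group does not deliver 527 completers, because the sample-size paragraph omits the clear-mammogram condition. The yield is about 356 to 516 per group and t-test power about 76% to 89%, on the assumption that between 69% and 100% of baseline responders attend and have a clear result. ANCOVA may restore 90% power, but that depends on a correlation the protocol does not give, and the stated count and its t-test basis are still not met. The step from 527 to 516 alone is not worth raising as an error.

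The selection is the more lasting issue, because a larger sample would not cure it. Up to about 98 non-attending baseline responders in the BC-Predict group could receive a risk letter and be absent from the 6-month comparison, assuming 69% attendance and 43% uptake among them. A between-group bias from this is possible and unquantified; the documents do not support saying that the comparison is biased.

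**What to change.** Send the 3- and 6-month questionnaires to all baseline responders, timed from the first offered appointment that the Procedure section already uses, whether or not they attended. Withhold them only where cancer has been diagnosed or assessment is pending. Report women with a clear mammogram as a subgroup. In the sample-size paragraph, restate the expected yield and power with the attendance assumption shown and, if ANCOVA is relied on, the assumed correlation.

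If the clear-mammogram condition is kept, say that the self-reported comparison, and the health-status data passed to the economic model, apply only to women with a clear mammogram. Restate the yield as 356 to 516. Keeping 527 completers under that condition would mean asking 527/(0.49 × 0.90) = about 1,196 per group at 90% attendance, or 527/(0.49 × 0.69) = about 1,559 at 69%.

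Cost of the preferred change: up to about 229 extra online questionnaires per group per round, to women who have already consented, plus rewording. Non-attenders may respond at less than 70%, so the yield could still fall below 516.
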